### Safety

An interim analysis will be performed for futility and safety after half of patients have completed the trial. The trial may be stopped if there is a statistically significant difference between the groups at the 5% level (two-sided test), and if with the statistician remaining blinded, the unblinded DMC recognizes that the effect is in the ‘wrong’ direction. This stopping rule will only have a minor effect on the type I error and power of the trial.

There will no statistical stopping rule for efficacy although the data monitoring committee (DMC) may suggest stopping the trial on the grounds of safety if there is an overwhelming positive effect of IVIg.

All causes of withdrawal from randomised treatment will be reported at days 22 and 43 post- randomisation. The prevalence of adverse events and reactions will be reported descriptively at 22 and 43 days post-randomisation. For patients an open-label infusion, AE’s reported from 43 to 85 days post-randomisation will be tabulated separately for reports rather than being reported with blinded AE’s.

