## Methods/Design

LIPS is a multicentre, randomised, double-blind, placebo-controlled, parallel group trial with an open extension. The parallel group design is an established research technique; the open extension is an optional trial element, where patients who have completed the parallel, blinded phase can request to receive one, or maximally two doses of IVIG ‘openly’, that is, assured that what they receive is IVIG (there is no placebo control). This extension is included to take account of service users’ preferences.

Blinding will be achieved by preparing both study drug and placebo (0.1% albumin in normal saline) solution into identical bottles. The albumin is added to achieve indistinguishable foaming and colour to the IVIg. Batch numbers and expiry dates for both the active and placebo drug will be indistinguishable.

For the time frame, study day 0 is defined as the day of randomisation, and a screening visit is scheduled maximally three weeks prior (day -21); patients then receive blinded infusions on days 1 and 22. Thereafter, in those who decide to receive open infusion on day 43 and day 64, pain diaries will be completed daily from day 43 to day 85 and then weekly for 9 weeks further to explore the duration of combined drug- and unspecific treatment effects (Additional file 1).

The sample size is 108 patients (54 patients per study arm). An interim analysis will be performed for futility and safety after half of patients have completed the trial. It will be suggested that the trial be stopped if there is a statistically significant difference between the groups in the ‘wrong’ direction at the 5% level (that is, one-sided test at the 2.5% level). This stopping rule will have a negligible effect on the type I error and power of the trial. There will no statistical stopping rule for efficacy although the DMC may suggest stopping the trial on the grounds of safety if there is an overwhelming positive effect of IVIg.

Clinical stopping rules will relate to unexpectedly poor recruitment and excessive withdrawals.

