#### Monitoring, quality control and assurance

The LIPS protocol has been developed with extensive review by clinicians, statisticians, and patient groups.

The LIPS Trial Coordination Centre will be based in the King’s Clinical Trials Unit in the Department of Biostatistics at the Institute of Psychiatry, King’s College London (IoP/KCL). Day to day management of LIPS will be the responsibility of the Chief Investigator and the Trial Manager. The Coordinating Centre will arrange meetings of the Trial Management Group (TMG) and Trial Steering Committee (TSC) and will coordinate independent Data Monitoring Committee (DMC) meetings.

The TMG will comprise [name] (Chair), the Trial Manager, the Data Manager, the Trial Statistician, and the manager of King’s Clinical Trials Unit. The TMG will arrange telephone conferences and provide monthly recruitment email updates during recruitment and status reports, and 6 monthly thereafter. The TMG will organise a meeting for all PIs (and for key staff working on the study) to sign the protocol, and to agree on the content and undergo training on SOPs before the start of recruitment. A second investigators’ meeting will be held at the end of the study to review the results. The TMG will also meet face-to-face every 6 months in Liverpool or London. The TMG will report to the Trial Steering Committee (TSC). All PIs will be kept informed of TSC and DMC advice and consulted by e-mail or teleconference as required.

The TSC will consist of an independent chair, two independent members, a site investigator, a patient representative, a nonvoting member, and the Chief Investigator; the names are detailed on page 4 of this protocol. The TSC will be responsible for approving the trial protocol and overseeing the conduct of the study, including advising on continuing or stopping the study in the light of advice from the DMEC. Meetings of the TSC will be held at least annually.

Membership of the DMEC will comprise an Independent Chair; an independent specialist with interest in neuropathic pain analgesic trials, and an independent statistician. The DMC will have access to the unblinded data and will monitor the progress of the trial in terms of safety and ethical issues. The DMC may advise the TSC to continue or to stop the trial according to pre-agreed upon stopping rules.

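### The interim procedure does not keep the statistician blinded: a significant two-sided result followed by continuation points strongly to a difference favouring IVIg

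*Protocol article*

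**What the plan says.** The Safety section places the interim at the halfway point: "An interim analysis will be performed for futility and safety after half of patients have completed the trial". The rule has two parts. The first is a test without direction: "The trial may be stopped if there is a statistically significant difference between the groups at the 5% level (two-sided test"). The second is that, "with the statistician remaining blinded, the unblinded DMC recognizes that the effect is in the" wrong direction. On benefit, the same section says: "There will no statistical stopping rule for efficacy". It allows the DMC to suggest stopping on safety grounds if the benefit is overwhelming.

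Methods/Design gives the same interim as a test in the wrong direction only ("that is, one-sided test at the 2.5% level") and does not say who runs it.

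On people, Statistical considerations assigns the data analysis to the study statistician. Monitoring, quality control and assurance lists the TMG as including "the Trial Manager, the Data Manager, the Trial Statistician". It gives the DMC access to unblinded data and a membership that includes a neuropathic pain specialist "and an independent statistician".

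**The concern.** The plan claims a property, a blinded statistician, that its procedure does not deliver in one important case. Whoever produces a two-sided p-value knows whether it is below 0.05. That person then learns whether the trial goes on. Because the trigger for stopping is significance in the wrong direction, and no efficacy rule stops the trial, significance followed by continuation leaves benefit as the likely explanation. If the data were analysed under coded arms, the sign of the estimate then identifies the codes as well.

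At stake is operational blinding in the second half of the trial. The Trial Statistician belongs to the group that manages the trial. On-site/central monitoring lets the data manager or statistician pick data fields for source checking, and Primary outcome measure leaves discrepancies between paper and text-message pain scores to be resolved. Such decisions should be made by people with no view of the interim effect.

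**Working it through.** **Inputs.** From Sample size calculation: difference 1.2 points, SD 2.2, 5% significance (taken as two-sided), 85% power, 10% loss, 5% noncompliance, correlation 0.7 over 37 measurements, total 108. From Randomisation: 1:1 allocation. From Safety: interim after half, so 54 patients, 27 per arm.

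**Reproducing the plan's own figures.**
- Per arm: 2 × (1.96 + 1.036)² × 2.2² / 1.2² = 60.4, rounded up to 61, total 122. This matches.
- Inflation to 152: 122/0.9 = 135.6, up to 136; 136/0.95² = 150.7, up to 151, then 152 to make it even. This is a reconstruction; the article does not show the step, and the plain 122/(0.9 × 0.95) = 142.7 does not give 152.
- Repeated-measures factor: (1 + 36 × 0.7)/37 = 0.708, and 152 × 0.71 = 107.9, so 108. This matches.

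**Chance of a significant interim result favouring IVIg.** By normal approximation, SE = SD × √(2/n per arm) and P = Φ(effect/SE − 1.96).

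| Assumption | SD | n per arm | SE | P at 1.2 | P at 0.6 |
|---|---|---|---|---|---|
| Plan's repeated-measures reduction, 2.2 × √0.708 | 1.85 | 27 | 0.504 | 66% | 22% |
| Same, with losses, 27 × 0.9 × 0.95 | 1.85 | 23.1 | 0.545 | 60% | 20% |
| No reduction | 2.2 | 27 | 0.599 | 52% | 17% |

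For the first row at 1.2: 1.2/0.504 = 2.38, and Φ(2.38 − 1.96) = 0.66. Under the null the figure is 2.5% in every row. At 1.55 points, the difference in the earlier crossover trial quoted in Background, the first row gives 87%.

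Two cross-checks:
- Taking final power as exactly 85%, the interim mean z is (1.96 + 1.036) × √0.5 = 2.12, and Φ(2.12 − 1.96) = 56%, inside the range.
- Combining the two unfavourable assumptions (SD 2.2 and 23.1 per arm) gives SE 0.648 and Φ(1.85 − 1.96) = 46%, a little below it.

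**Chance of a significant result in the wrong direction at 1.2 points.** Φ(−2.38 − 1.96) is about 0.001%.

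**How firmly continuation reveals direction.** Let c be the chance that the trial continues despite a significant wrong-direction result. The documents do not give c, so it is an assumption. Ignore stops for overwhelming benefit. Then P(favours IVIg | significant, continues) = P(favour) / [P(favour) + c × P(wrong)].
- Under the null the two tails are equal, so this is 1/(1 + c): 91% at c = 0.1 and 67% at c = 0.5.
- At 0.6 points it is 0.2209/(0.2209 + 0.00081c), at least 99.6% for any c.

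The advisory wording therefore weakens the inference appreciably only when the true effect is close to zero.

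**The case against.** Several points on the other side stand.

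- **Who runs the test is not stated.** It is inferred from the contrast between a blinded statistician and an unblinded DMC, and from the sections naming the study statistician and the Trial Statistician, who are not expressly the same person. If the DMC's statistician already computes the test and nobody else sees it, nothing leaks.
- **Stopping is advisory.** Safety says the trial may be stopped, and Methods/Design says stopping will be suggested. The DMC may also suggest stopping for overwhelming benefit. Continuation is strong evidence of direction, not proof, and some significant favourable results would not be followed by continuation.
- **The reach is limited.** The leak is to one person, and nothing says the p-value is passed to the rest of the TMG. Patients score their own pain, sites stay blinded, and the outcome window, model type, centre adjustment and handling of missing data are already stated.

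A reader might infer that Methods/Design and Safety contradict each other, one being one-sided and the other two-sided. They do not: a two-sided 5% result that must also lie in the wrong direction is the one-sided 2.5% rule. A reader might also infer that the interim reveals that IVIg works. That is too strong, because it would suggest only a nominally significant difference at half the sample. Nor do the percentages describe the share of successful trials; they are chances given an assumed true effect.

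One objection does not hold: that this is charter detail an article may omit. The article itself asserts the blinding and describes the step meant to secure it.

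**Conclusion.** The concern holds in this form: if the trial statistician produces the two-sided interim test, the blinding claimed in Safety fails whenever the result is significant and the trial continues. At the design effect, a significant favourable result is more likely than not under the plan's own variance model (66%, or 60% with losses) and about even without the repeated-measures gain (52%). These are slight upper figures for the full sequence, since a stop for overwhelming benefit would remove some of it. The chance falls to about 22% at half the design effect and 2.5% under the null.

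The stopping boundary, type I error and power are not affected. The conclusion rests on the inferred operator and on the harm rule being followed as a rule in practice.

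**What to change.** Reword the Safety section so that:
- the DMC's existing independent statistician runs the comparison in the harm direction only, one-sided at 2.5% as in Methods/Design, with the allocation file sent directly to the DMC;
- the trial statistician supplies only analysis code tested on dummy allocations, and sees no interim p-value;
- the TMG and Trial Steering Committee receive only a continue or stop message;
- the statistical analysis plan is signed off before the interim.

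Continuation would then tell the trial statistician only that no significant harm prompted a stop. The boundary is the same 2.5% tail, so type I error and power do not change. The cost is a few hours' work for an existing DMC member, and the wording to go with it.

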### Sample size calculation

The sample size was calculated as follows: 122 participants are required to detect a difference in pain score of 1.2 using a two-sample t-test assuming 5% statistical significance, 85% power and a common standard deviation of 2.2 (as in our previous study (8)). Assuming 10% loss to follow-up and 5% noncompliance increases, this number increases to 152 participants. We actually intend to collect 37 measurements of pain intensity (the primary outcome) per participant and analyse the outcome using a mixed-effects regression model.

Thus we can reduce this sample size based on these extra measurements. The correlation among a patient’s measures is assumed to be 0.7 (from our previous study), and hence, the multiplying factor is as follows:

Therefore, the total required sample size is 152 × 0.71 = 108 participants [26].

### Compliance and withdrawal

#### Subject compliance

Compliance will be measured by attendance at infusion visits on day 1 and day 22 and tolerance of entire prescribed infusion.

#### Treatment cessation

Patients who develop an unexpected new condition precluding further participation will be withdrawn from receiving further infusions, but will continue to complete daily pain diaries and asked to attend for collection of other outcome data (intention to treat). If patients do not tolerate blinded infusion 1, they may still be administered blinded infusion 2 if both the patient and clinician are agreeable.

#### Withdrawal of participants

Study drug must be discontinued for the following:the participant decides he/she no longer wishes to continue;withdrawal is recommended by the Investigator or another clinician (for example, intercurrent illness during course of study or side effects from study drug); orthe trial is terminated at the request of the DMC.

Patients will be discontinued for the following:they are randomized, but never receive any drug (that is, the first infusion is never started - this is also termed ‘non-compliance’) orthey do not provide any values for the day 6 to 43 outcome pain diary data (this is also termed ‘missing data’).

Participants have the right to withdraw from the study at any time and for any reason without providing a reason. The investigator also has the right to withdraw participants from the study if they consider that it is in the best interests of the participant. Should a participant decide to withdraw from the study, he/she will be asked to volunteer a reason for withdrawal but are at liberty not to state a reason.

Should a participant withdraw from study drug only, efforts will be made to continue to obtain follow-up data with the permission of the patient. Subjects who withdraw from treatment early will be encouraged to return to the study site for follow-up until day 43, providing that consent is not withdrawn.

### Data monitoring, quality control and quality assurance

#### Discontinuation rules

The trial may be prematurely discontinued on the basis of predefined stopping criteria, or for other reasons given by the independent Data Monitoring and Ethics Committee, study sponsor, regulatory authority or ethics committee concerned.

#### Monitoring, quality control and assurance

The LIPS protocol has been developed with extensive review by clinicians, statisticians, and patient groups.

The LIPS Trial Coordination Centre will be based in the King’s Clinical Trials Unit in the Department of Biostatistics at the Institute of Psychiatry, King’s College London (IoP/KCL). Day to day management of LIPS will be the responsibility of the Chief Investigator and the Trial Manager. The Coordinating Centre will arrange meetings of the Trial Management Group (TMG) and Trial Steering Committee (TSC) and will coordinate independent Data Monitoring Committee (DMC) meetings.

The TMG will comprise [name] (Chair), the Trial Manager, the Data Manager, the Trial Statistician, and the manager of King’s Clinical Trials Unit. The TMG will arrange telephone conferences and provide monthly recruitment email updates during recruitment and status reports, and 6 monthly thereafter. The TMG will organise a meeting for all PIs (and for key staff working on the study) to sign the protocol, and to agree on the content and undergo training on SOPs before the start of recruitment. A second investigators’ meeting will be held at the end of the study to review the results. The TMG will also meet face-to-face every 6 months in Liverpool or London. The TMG will report to the Trial Steering Committee (TSC). All PIs will be kept informed of TSC and DMC advice and consulted by e-mail or teleconference as required.

The TSC will consist of an independent chair, two independent members, a site investigator, a patient representative, a nonvoting member, and the Chief Investigator; the names are detailed on page 4 of this protocol. The TSC will be responsible for approving the trial protocol and overseeing the conduct of the study, including advising on continuing or stopping the study in the light of advice from the DMEC. Meetings of the TSC will be held at least annually.

Membership of the DMEC will comprise an Independent Chair; an independent specialist with interest in neuropathic pain analgesic trials, and an independent statistician. The DMC will have access to the unblinded data and will monitor the progress of the trial in terms of safety and ethical issues. The DMC may advise the TSC to continue or to stop the trial according to pre-agreed upon stopping rules.

The Principal Investigators will be responsible for the day-to-day study conduct at site. This includes establishing and carrying out the trial at his/her centre in accordance with international, national and local law and regulations and GCP. They will ensure that all site specific documentation is complete and correct; and that all staff involved in the trial are compliant with Trust, GMC and other relevant regulations, and that they are appropriately trained in those aspects of GCP relevant to their role in the study whilst being familiar with the trial protocol.Principle Investigators are also responsible for managing recruitment on target and collecting and submitting accrual and outcome data in a timely manner; responding in timely fashion to requests from the Trial Coordinating Centre for information; providing and responding promptly to SAE and suspected unexpected serious adverse reaction (SUSARs) reports; agreeing to monitoring and audit visits as required.

Central and site monitoring of study conduct and data collected will be performed by the Trial Manager at the KCTU on behalf of the Sponsor. Full details will be documented in a monitoring plan, agreed upon with the study sponsor. The main areas of focus will include consent, serious adverse events, essential documents, and drug accountability and management. All monitoring findings will be reported and followed up with appropriate persons in a timely manner.

The study may also be subject to audit or inspection by the University of Liverpool or the Walton NHS Trust under their remit as co-sponsors, or by MHRA or other regulatory bodies to ensure adherence to GCP and regulatory requirements.

### Direct access to source data and documents

The investigators agree to provide full access to all source data, study data and materials to the trust research governance department, ethics committee, regulatory authority and trial manager for purposes of monitoring, audit or inspection.

### Pharmacovigilence

#### Expected adverse reactions

Adverse event reporting will be in compliance with GCP. Most adverse drug reactions that occur in this study, whether serious or not, will be expected treatment-related side effects as IVIg has a well-established side-effect profile.

IntratectTM can cause adverse reactions such as chills, headache, fever, vomiting, allergic reactions, nausea, arthralgia, low blood pressure and mild back pain, which may occur occasionally.

Rarely, human normal immunoglobulins may cause a sudden fall in blood pressure, and in isolated cases, anaphylactic shock, even when the patient has shown no hypersensitivity to previous administration.

Cases of reversible aseptic meningitis, isolated cases of reversible haemolytic anaemia/haemolysis, and rare cases of transient cutaneous reactions have been observed with human normal immunoglobulin.

Increase in serum creatinine level and/or acute renal failure have been observed.

Very rarely, thromboembolic reactions, such as myocardial infarction, stroke, pulmonary embolism, and deep vein thromboses have occurred.

Details of further spontaneously reported adverse reactions include the following:cardiac disorders: angina pectoris (very rare);general disorders and administrations site conditions: rigors (very rare);immune system disorders: anaphylactoid shock (very rare), hypersensitivity (very rare);investigations: blood pressure decreased (very rare);musculoskeletal and connective tissue disorders: back pain (very rare);respiratory, thoracic and mediastinal disorders: dyspnoea NOS (very rare); orvascular disorders: shock (very rare).

The adverse events reported above are expected in the sense that they are possible known side-effects of the study medication, but all reported instances of both serious and non-serious adverse events will be reported in this study.

During the trial, investigators will be made aware of any updates to the summary of product characteristics (SPC) but the protocol need not be amended every time there is a change unless it directly affects the study conduct. The source of accurate information regarding the active medication must always be the SPC and not the study protocol, and the above information is provided to reflect the situation at study start only.

### Protocol specifications

#### For purposes of this protocol

Any serious adverse events will be recorded throughout the duration of the trial until 21 days after cessation of study drug or until resolution.Non-serious adverse events will be recorded throughout duration of trial until 21 days after cessation of study drug.Serious adverse events exclude any pre-planned hospitalisations not associated with clinical deterioration.

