## Background

Complex regional pain syndrome (CRPS) is a post-traumatic pain in a limb, associated with sensory, motor, autonomic, skin and bone changes [1, 2]. CRPS can resolve spontaneously, but if a spontaneous resolution does not occur early, it is less likely to occur later. Many patients with CRPS have no effective method to relieve their ongoing pain [3]. Those patients with CRPS of moderate to severe pain intensity, the target group for this study, report on average a very poor quality of life, and they usually cannot work [4]. Immunoglobulin treatment for chronic pain is a novel technology [5]. In one of the first open trials, we found that low dose intravenous immunoglobulin (IVIg) may be effective in some patients with CRPS (for 11 participants: three had >70% pain relief, two had >25% but < 70%, and six had 0 to 25%, following a variable number of low-dose infusion repeats) [6]. We later showed that in one patient repeat treatments provided reproducible effects [7]. Recently, we confirmed in a UK single-centre crossover, randomised, placebo-controlled trial (RCT) [8], that a single, low dose (0.5 g/kg) infusion of IVIg significantly reduced pain in patients with CRPS (n = 13, pain intensity on a validated 11-point numeric rating scale (NRS) higher than 4 (NRS 0 = no pain, 10 = pain as bad as you can imagine [9]); these patients had a disease duration of 0.5 to 2.5 years. The treatment difference was 1.55 NRS points (95% CI: 1.29 to1.82, *P* <0.001). In a responder analysis (12 patients had received treatment), three patients had ≥50% less pain (4.5, 5 and 5 NRS points) after IVIg when compared with after saline treatment, and two patients had 2 and 2.5 NRS points less pain (29% and 31% less pain). One patient had 2 NRS points less pain (25% less pain) after saline compared with after IVIg treatment. The average effect duration was 5 weeks. There was also a significant overall reduction of CRPS-related, non-painful symptoms and, in responders, improved sleep and global improvement, with few adverse events (headaches and pain increases for <3 days). Post-infusion questionnaires showed successful blinding of patients and study doctors.

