### Definition of end of study

The end of the study will be the last participant’s final study contact at day 148 (for those who elect to receive open label infusions) or at day 64 (for those who elect not to receive open label infusion).

SAEs will be monitored for 21 days after final dose of IVIg or until resolution.

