### Administration of investigational medicinal product

If centres prefer to run a slower infusion than described above, this will not be considered a protocol violation.

Patients may be offered paracetamol 1 g orally during the infusion, where clinically indicated. Patients are under continuous nurse observation during the infusion; in cases where no reduction of the infusion rate is required, the infusion duration for a participant of 75 to 85 kg body weight is about 4.5 hours.

In the event that patients do not receive their entire first infusion, either due to having to stop early because of time constraints arising from long infusion duration with a low rate, or because side effects are intolerable even with the lowest infusion rate, they should still be offered the second infusion, as patients often tolerate second infusions better. Details of the amount infused should be recorded in the medical notes and electronic Case Report Form (eCRF).

Where the infusion cannot be tolerated and the patient wishes to not receive additional infusion, the patient is withdrawn from further infusion, but follow-up data will be collected until the end of the study.

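### Adverse-event recording ends 21 days after each patient's last dose, which matches the fixed reporting days only on the full infusion schedule; day 43 has no onset rule, and the two SAE windows use different anchors

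*Protocol article*

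**What the plan says.** Under Protocol specifications (For purposes of this protocol), non-serious "adverse events will be recorded throughout duration of trial until 21 days after cessation of study drug". For serious events the rule is: "Any serious adverse events will be recorded throughout the duration of the trial until 21 days after cessation of study drug or until resolution".

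The Safety section fixes the reporting days: "The prevalence of adverse events and reactions will be reported descriptively at 22 and 43 days post-randomisation". For patients who have an open-label infusion, events "reported from 43 to 85 days post-randomisation will be tabulated separately for reports rather than being reported with blinded" events.

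Definition of end of study gives a second SAE rule: "SAEs will be monitored for 21 days after final dose of IVIg or until resolution".

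Patients who stop infusions stay in the trial. Under Administration of investigational medicinal product, after intolerance "the patient is withdrawn from further infusion, but follow-up data will be collected until the end of the study". Treatment cessation continues the diaries and other outcome data, and Withdrawal of participants encourages follow-up to day 43.

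**The concern.** The end of recording depends on each patient's last dose, while the reporting days are fixed. Tolerability can shorten dosing, so treatment can shorten the period in which events are recorded. The by-arm figure at day 43 may then cover different lengths of observation for different patients. The documents do not settle whether the continued follow-up of early stoppers includes adverse events.

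Two boundaries are also loose. Day 43 is a blinded reporting point, the first day of the open-label table and the day of the first open-label infusion, yet no rule separates events before that infusion from events after it. And a placebo patient who declines open label never has a final dose of IVIg, so the SAE rule in Definition of end of study gives that patient no window.

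The short-term risk profile is a stated secondary objective and each arm has 54 patients, so a few unrecorded or misplaced events would show. A later analysis plan can choose a denominator, but it cannot recover events that were never recorded.

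**Working it through.** **Inputs.** Blinded infusions on days 1 and 22, with the first allowed as late as day 5 (Methods/Design; Selection and timing of dose for each participant). Open-label dosing on day 43 only, or on days 43 and 64 (Dispensing and distribution of investigational medicinal product). Recording to last dose + 21 days. Reporting at days 22 and 43, and an open-label table for days 43-85 (Safety). Sample size 108.

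**Step 1: the plan's own days.** On the full schedule, 1+21=22, 22+21=43 and 64+21=85. These are exactly the reporting limits, so there is no mismatch.

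**Step 2: other dosing patterns allowed by the protocol.**

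| Infusions received | Window ends | Reporting runs to | Days outside the window |
|---|---|---|---|
| Day 1 only, no open label | 1+21 = 22 | 43 | 23-43 (21 days) |
| Day 5 only, no open label | 5+21 = 26 | 43 | 27-43 (17 days) |
| Both blinded, no open label | 22+21 = 43 | 43 | none |
| Open label on day 43 only | 43+21 = 64 | 85 | 65-85 (21 days) |
| Open label on days 43 and 64 | 64+21 = 85 | 85 | none |

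**Step 3: size for early stoppers.** The documents give no rate of stopping after one infusion and no expected adverse-event incidence, so both are assumed. Let p be the share who stop after one infusion and take no open-label dose, and T the true cumulative incidence over the 42 days from day 1 to day 43. Assume a constant hazard and keep all patients in the denominator.

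- Hazard: h = -ln(1-T)/42.
- Recorded incidence: (1-p) × T + p × (1 - exp(-21h)).
- Shortfall: p × [T - (1 - √(1-T))].
- With T = 30%: 1 - √0.70 = 0.1633, so the shortfall is p × 0.1367.

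| p | Patients of 108 | Person-time lost (p × 21/42) | Recorded incidence | Shortfall, percentage points |
|---|---|---|---|---|
| 2% | 2.2 | 1.0% | 29.7% | 0.3 |
| 5% | 5.4 | 2.5% | 29.3% | 0.7 |
| 10% | 10.8 | 5.0% | 28.6% | 1.4 |
| 20% | 21.6 | 10.0% | 27.3% | 2.7 |

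For the same range of p, T = 10% gives 0.1 to 1.0 points and T = 50% gives 0.4 to 4.1 points.

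**Step 4: day 43.** The Safety section places events by when they are reported, not by when they began. An event that began after the day-22 infusion but was first reported at the day-43 visit meets the wording for the open-label table. So does an event on day 43 before the infusion starts. Both belong to the randomised period.

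**Step 5: SAE anchors.** Definition of end of study counts from the last IVIg dose, and Protocol specifications counts from the last dose of study drug. For a placebo patient without open label, only the second gives a date. Blinded site staff cannot apply the first to any patient who declines open label.

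**The case against.** The 21-day window equals the dosing interval and fits the planned schedule exactly. Early stoppers remain in follow-up, adverse events are among the listed measures (with times in an additional file that is not shown), and the section on recording serious events says that all adverse events should be recorded. A patient who misses the second blinded infusion but takes open label has a later last dose, and so no such gap before day 43. The event that causes a patient to stop normally falls inside the 21 days. All this stands and keeps the effect small. It does not remove the conflict: the general instruction gives no end date, whereas the dose-anchored rule does.

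A reader might infer more than the documents support:

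- **That early stoppers are counted without being observed.** No denominator is stated, and follow-up continues. The passages conflict, but they do not show that these patients go unobserved.
- **That prevalence is reported at day 85.** It is not. Days 43-85 are only the range of a separate tabulation.
- **That day-43 infusion reactions inflate the placebo rate or are counted twice.** For open-label patients the two tables are exclusive by the plan's wording. The remaining ambiguity mainly takes events out of the blinded table.
- **That 21 days is too short.** The 5-week figure in the Background is the average duration of effect, and the 3-month figure under Concomitant medications concerns live vaccines. Neither is a latency for adverse events.

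The IVIg anchor may be no more than loose wording, but the two SAE rules still differ.

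**Conclusion.** The concern holds as a minor fault in the safety rules. Taken literally, non-serious recording ends before day 43 for a patient with one blinded infusion and no open-label dose, and before day 85 for a patient with one open-label dose. Day-43 events have no onset rule, and the two SAE windows have different anchors.

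The understatement of a 30% day-43 incidence would be about 0.3 to 2.7 percentage points for 2 to 20% stopping. This rests on assumed rates, a constant hazard and no adverse-event recording after the window closes. If events cluster soon after infusions, the loss is smaller. The effect on the difference between arms has no established direction, because the documents do not say how stopping would divide between arms. The number of events that could move at day 43 cannot be estimated from the documents. The primary analysis is not affected.

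**What to change.** - **Protocol specifications:** record adverse events to day 43 for every patient who received any trial infusion, however many were given, and to day 85 for every patient who received an open-label dose. State that the continued follow-up described for patients who stop infusions includes adverse events.
- **Safety:** assign events by onset. Events that begin before the start of the day-43 open-label infusion belong to the blinded table, and later ones to the open-label table.
- **Definition of end of study:** reconcile the SAE anchor with Protocol specifications by counting from the last dose of study drug.

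The cost is wording in three sections, slightly more adverse-event recording, and an onset time on the eCRF for day-43 events. Patients who were never infused are discontinued under Withdrawal of participants and are not affected.
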